***End-point evaluation***

**Neurocognitive evaluation**

The neurocognitive evaluation will be done at baseline and after 2 months for all patients. In the cross group a 3^rd^ evaluation will be performed after 4 month- after crossing and completing 2 months of HBOT treatment. Cognitive function will be assessed using the one-hour Mindstreams Computerized Cognitive Test Battery (Mindstreams; NeuroTrax Corp., NY). Detailed description of the tests can be found on Neurotrax website ([www.neurotrax.com](http://www.neurotrax.com)).

To minimize differences in age and education, each outcome parameter will be normalized and fit to an IQ-like scale (mean=100, S.D=15) according to patient's age and education. Normalized subsets of outcome parameters will be aggregated to produce four index scores relevant to mild TBI: **Memory, Attention, Executive function,** and **Information Processing Speed**.

Three different test versions exist in the Mindstreams testing battery to allow repeated administrations, test-retest reliability for those versions were evaluated and found high, with no significant learning effect [[23](#_ENREF_23),[24](#_ENREF_24)].

**Brain functional Imaging - SPECT imaging and Analysis**

Single photon emission computed tomography (SPECT) will be conducted before and after HBOT. Subjects will lay supine in a quiet dimly lit room for 20 min prior to injection of the radiopharmaceutical. Apart from administration of the injection by a physician, they will remain alone in the room during this period. Subjects will be asked to remain at rest for 10 min after the injection of the radiopharmaceutical to allow uptake of the radiopharmaceutical in the brain.

An injection of 925-1110 MBq (25-30 mCi) of technetium-99m ethyl cysteinate dimmer (Tc-99m-ECD) will be given into an arm vein through a previously placed intravenous cannula. SPECT imaging of the brain will be performed, at 40-60 min post injection, with the subject’s head supported by a headrest, using a dual detector gamma camera (ECAM or Symbia T, Siemens Medical Systems) equipped with high resolution collimators. Data will be acquired in the step-and-shoot mode, using a 360 degree circular orbit, with the detectors of the gamma camera as close as possible to the subject’s head. The camera used for imaging will be noted for each subject and the same camera will be used for the follow-up study. Data will be acquired using a 128׳128 image matrix in 3 degree steps of 20 seconds per step. Data will be reconstructed by iterative reconstruction with no filtering. The Chang method (*μ*=0.12/ cm) will be used for attenuation correction.

Intra subject visual analysis will be conducted using a process in which pre and post treatment studies are fused and normalized to pre-treatment whole brain activity.

Visual analysis will be carried out by two nuclear medicine physicians who compared the scans independently and grad them as either: 1=no change, 2=mild change and 3=significant change. Where, no change is assign when no visual difference is noted in the number or size of perfusion deficits, mild change is given when a reduced number of perfusion defects are noted or the size of the perfusion defects is reduced. Significant change should be attributed when a global perfusion increment is observed in addition to diminution of defect numbers or size. Differences in evaluation will be resolve after reviewing the images together. Scan visual interpretation will be carried out while blinded to any laboratory or clinical data.

A comparison of the SPECT results with anatomical imaging (CT or MRI) will be done in order to evaluate the extent of perfusion deficit in relation to the anatomical lesion.

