**Objectives**

The aim of the current study is to evaluate, for the first time in a prospective cross-over, randomized study, the effect of hyperbaric oxygen therapy (HBOT) on patients with chronic neurocognitive deficiency due to mild TBI.

- The primary endpoints of the study are to evaluate the effects of the HBOT on:
- Neurocognitive function (using Mindstreams neurocognitive battery)
- Brain metabolism (as visualized by SPECT)
- The secondary endpoints included quality of life evaluation.

The safety of the HBOT in this post TBI population will also be evaluated and any adverse event will be recorded.

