***Study protocol***

After signing the informed consent, patients will be randomized in 1:1 manner into the treated or the control-cross group. After the randomization, patients will be invited for baseline evaluation that will include full review of their medical status and complete physical examination. All patients will present baseline anatomical scan (CT/MRI). After their inclusion, patients will be randomized to two groups: a treated group and a cross group. All patients will go through evaluation of their neurocognitive function using neurocognitive testing battery, quality of life using EQ-5D questionnaire and brain functional imaging (rCBF-SPECT scan). The patients in the treated group will be evaluated twice – at baseline and after 2 months of HBOT treatment. The patients of the cross group will be evaluated three times – at baseline, after a 2 month control period of no treatment and after a consequent 2 month period of HBOT treatment. We emphasize that the study will be a cross-over trial and patients in the cross group will receive HBOT treatment after their second evaluation and will go through a third neurological evaluation after the cross, when they will complete their HBOT.

The following HBOT treatment protocol will be practiced: The patients will go through 40 HBO treatments (each treatment session will be given on a separate day), distributed over two months (five days a week). Each session will be for 60 minutes in 100% oxygen atmosphere and at pressure of 1.5 ATA.

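### The SPECT section defines a reading only for pre- versus post-treatment pairs, leaving the cross group's control-period pair without a reading rule and its reference scan unnamed

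*Protocol*

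**What the plan says.** The Objectives of the protocol name two primary endpoints: the Mindstreams neurocognitive battery and brain metabolism on SPECT.

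Under Study protocol, "patients will be randomized in 1:1 manner into the treated or the control-cross group". SPECT is listed there among the evaluations that all patients undergo. The schedule then differs by arm. "The patients in the treated group will be evaluated twice", once before HBOT and once when it is finished. For the other arm the text reads "The patients of the cross group will be evaluated three times". Its second evaluation closes the two untreated months, and its third follows the HBOT course given after the cross.

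The section on SPECT imaging and analysis gives its own timing: "Single photon emission computed tomography (SPECT) will be conducted before and after HBOT". It refers to a single follow-up study, for which the same camera is to be used. For the reading, it describes a process in which "pre and post treatment studies are fused and normalized to pre-treatment whole brain activity". Two nuclear medicine physicians then grade the change as none, mild or significant. The two upper grades both describe improvement (fewer or smaller defects, with or without a global rise in perfusion). No grade describes deterioration. Readers are to be blinded to laboratory and clinical data.

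By contrast, the Neurocognitive evaluation section sets out its time points by arm: baseline and 2 months for everyone, and a third test at 4 months in the cross group.

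**The concern.** The SPECT grade is a change score: it exists only for a pair of scans that somebody has read. The cross group's first two scans have no treatment between them, so they are not a pre- and post-treatment pair, and the reading rule does not reach them. If the imaging team follows the SPECT section, each patient contributes one graded pair, and that pair always spans HBOT.

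Three things are then at stake.

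- **The randomised comparison.** The natural controlled contrast is two months of HBOT in the treated group against two untreated months in the cross group. It needs a grade for the untreated pair.
- **The meaning of an improved grade.** The scale can record no change or improvement but not worsening. Random variation between two scans can therefore show up only as nothing or as benefit. Graded untreated pairs would show how often that happens.
- **The masking.** If every pair read brackets HBOT, the readers know that treatment came between the scans, even without clinical data. Expectation then has a route into a visual grade.

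**Working it through.** The point does not rest on a sample size, power or alpha, and the plan gives no figure for it to reproduce. The check is a count of scans and pairs under the two sections, followed by the consequence for the estimate.

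**Step 1. Scans and consecutive pairs per patient.** With k scans there are k − 1 consecutive pairs.

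| | Treated group | Cross group |
|---|---|---|
| Scans due (Study protocol) | 2 | 3 |
| Consecutive pairs available | 2 − 1 = 1 | 3 − 1 = 2 |
| Pairs covered by the pre/post-treatment reading | 1 | 1 |
| Pairs with no reading rule | 1 − 1 = 0 | 2 − 1 = 1 (baseline to month 2) |

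**Step 2. How many patients.** Allocation is 1:1. The only sample size stated is N = 31 (Sample Size Considerations), and the text does not say whether this is the total or the number per group. If it is the total, 31 / 2 = 15.5, so 15 or 16 cross-group patients have a pair without a rule. If it is per group, 31 do.

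**Step 3. Which scan is the reference in the cross group.** The section normalises to pre-treatment activity, but this group has two pre-treatment scans.

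- Baseline as reference: the pair runs from month 0 to month 4, which is 2 untreated months plus 2 months of HBOT.
- Month 2 as reference: the pair runs from month 2 to month 4, which is 4 − 2 = 2 months, all HBOT.

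Only the second covers the same kind of interval as the treated group's pair. The text does not choose between them.

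**Step 4. What the estimate contains.** Let t be the proportion of HBOT pairs graded mild or significant change, and b the proportion of untreated pairs that the same readers would grade that way.

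- Reading as written: the result reported is t.
- Controlled reading: the result is t − b.
- Difference: t − (t − b) = b.

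Because the scale has no grade for worsening, chance shifts in the unfavourable direction cannot cancel those in the favourable direction, so b need not be zero. The protocol gives no scan-rescan or reader-agreement figure from which b could be obtained.

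**Step 5. Does another section supply the rule?** The Randomization section says that blinded evaluation can be assured for SPECT and that the cross allows efficacy to be assessed within each group. Neither statement says that the control-period pair is read, or against which scan. The Primary Efficacy Analysis section deals with the neurocognitive score only.

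**The case against.** A reader might infer that the SPECT section contradicts the three-evaluation schedule and that control-period scans would not be taken. The text does not support that. Scanning before and after HBOT is compatible with two earlier scans and one later one, the sentence does not say only, and the Study protocol section plainly schedules the middle scan. This is a mismatch to reconcile.

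A reader might also infer that the control pair will never be graded and that the endpoint has no control. That too goes beyond the text. No sentence forbids grading the pair. The grade definitions are written in terms of perfusion defects and could be applied to it unchanged. The control scans will exist and could be read at any time. The trial is described as randomised and controlled, and offering blinded SPECT evaluation as an answer to unblinded patients suggests that the sponsor may have meant to use the control-period scans.

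It can further be said that the choice of contrast belongs in an analysis plan that is not at hand. That is fair for the choice of test. It does not dispose of the point, because the protocol itself fixes the timing, the pairing, the normalisation and the grading, and does so for treatment pairs alone. An analysis plan cannot compare grades that the imaging procedure does not produce.

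What stands of the objection is that the control exists by design. What is missing is a rule for reading it.

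**Conclusion.** The point holds as a gap in the reading rule for a primary endpoint. Followed as written, the SPECT section yields within-patient change across HBOT and no grade for the control period, and it leaves the cross group's reference scan open between a 2-month and a 4-month interval.

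The extent is certain: one consecutive pair per cross-group patient, so 15 or 16 pairs if 31 is the total and 31 if it is the number per group. The effect on the result is the untreated improvement proportion b. It cannot be derived from the document, and any value put on it would simply be returned as the answer.

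The conclusion assumes that the readers grade the fused pairs that the section describes, which is its natural reading. If the sponsor always intended to grade the untreated pair, the change below only makes that explicit. If not, it restores the randomised comparison for this endpoint. It should be settled before any scans are read.

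**What to change.** Revise the SPECT section as follows.

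1. List the SPECT time points by arm, as is already done for the neurocognitive test: baseline and month 2 in both groups, plus month 4 in the cross group.
2. Name the graded pairs: baseline to month 2 in both groups, and month 2 to month 4 in the cross group. Normalise each pair to its earlier scan.
3. Have the same two readers grade all pairs in mixed random order, masked to arm and to interval.
4. Make the treated versus cross grade at month 2 the controlled SPECT comparison, with the within-group change over HBOT as supportive evidence.

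The cost is a few sentences and one extra pair reading per cross-group patient: 15 or 16 pairs if 31 is the total, 31 if it is per group. As two physicians read each pair, that is 30 to 32, or 62, individual readings. The scans are already required by the Study protocol section, so no new scans or staff are needed.

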**Randomization**

Since the diversity of the patients included in the study, after signing the informed consent is expected to be high, no stratifies criteria will be used. Patients will be randomized in 1:1 fashion to either treatment or controlled-cross group.

There will be no placebo in the cross group during the control period. The only way to give “placebo” of HBOT, is to bring the patients to the hyperbaric chamber and to increase the environmental pressure in a way the patients will “feel the hyperbaric pressure” in their ears. However, Henry’s law states: “the amount of a given gas dissolved in a given type and volume of liquid is directly proportional to the pressure of that gas in equilibrium with that liquid”. Thus, hyperbaric environment significantly increases the dissolved oxygen pressure even if a person holding his breath [[29](#_ENREF_29)]. Moreover, the alternative of hosting the patients in the hyperbaric chamber without any pressure increase cannot serve as a real placebo since the patients will not feel the pressure. Accordingly, the only real “placebo” could be achieved by increasing the pressure and reducing the percentages of the oxygen but that holds significant safety consideration.

From the ethical point of view, it is deemed unethical to “treat” the patients (40 sessions in the hyperbaric chamber) while they actually know that it is a placebo. In order to somewhat compensate for this limitation, the control will be a cross group and after the 2^nd^ evaluation at the end of a control period they will be crossed to HBOT. The cross for treatment enables intra-group efficacy evaluation in both treatment and control group.

Since the patients will know they are not receiving HBOT during the control period they will not be blinded with regard to the treatment arm. Accordingly, the quality of life evaluations will not be blinded. However, the complete blindness evaluation can be assured in both of the primary end points of this study, The Mindstreams computerized evaluation and the brain SPECT evaluation done by the radiologist.

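### The SPECT primary endpoint has no grade for worsening, its top grade needs a global increase that the normalisation removes or confounds, and masking to scan order and arm is not described.

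*Protocol*

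**What the plan says.** Under Objectives, the protocol names "Brain metabolism (as visualized by SPECT" as one of two primary endpoints. The section on brain functional imaging fixes how it is scored. Two nuclear medicine physicians independently grade each patient's pair of scans "1=no change, 2=mild change and 3=significant change" and settle differences together. The three grades are defined as follows:

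- Grade 1: "no change is assign when no visual difference is noted in the number or size of perfusion deficits".
- Grade 2: "mild change is given when a reduced number of perfusion defects are noted or the size of the perfusion defects is reduced".
- Grade 3: "Significant change should be attributed when a global perfusion increment is observed in addition to diminution of defect numbers or size".

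For the comparison, "pre and post treatment studies are fused and normalized to pre-treatment whole brain activity". The tracer instruction reads "An injection of 925-1110 MBq (25-30 mCi", with imaging 40 to 60 minutes later and the same camera used at follow-up. Readers are masked to laboratory and clinical data; scan order and treatment arm are not mentioned.

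The Randomization section explains why there is no placebo and then states that "the complete blindness evaluation can be assured in both of the primary end points of this study". It adds that the crossover allows efficacy to be evaluated within each group. According to the Study protocol section, patients are randomised 1:1, and the cross group is evaluated at baseline, after two untreated months, and again after HBOT.

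**The concern.** The scale runs in one direction only. A pair that looks worse is not a pair without visible difference, and it is not a reduction in defects, so none of the three definitions fits it. The reader must either score it 1, against the definition, or leave it ungraded. Either way, noise that is symmetric on the images becomes one-sided in the data, and a real loss of perfusion after HBOT could not be recorded.

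The step from grade 2 to grade 3 depends on a whole-brain increase, while the images are first normalised to whole-brain activity. It is unclear that the reader can see the quantity being graded.

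Finally, the protocol offers blinded reading of the primary endpoints in place of a placebo. If readers know which scan came later, expectation acts in the only direction that the scale can record.

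**Working it through.** The protocol attaches no effect size, power or alpha to SPECT, so there is no stated figure to reproduce. The check has three parts.

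**1. Directions covered by the grades**

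| What the reader sees | Grade under the definitions |
|---|---|
| No difference in number or size of defects | 1 |
| Fewer or smaller defects | 2 |
| Fewer or smaller defects plus a global increase | 3 |
| More or larger defects | none |
| Global decrease | none |
| Global increase without fewer or smaller defects | not clearly placed |

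To see the effect, assume no true change, with a share b of pairs looking better by chance and the same share b looking worse. The noise rates are assumptions; the protocol gives none.

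- Worsened pairs scored 1: share recorded as improved = b.
- Worsened pairs left ungraded: share recorded as improved = b / (1 − b).

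| b | Scored 1 | Ungraded | True net change |
|---|---|---|---|
| 10% | 10% | 0.10/0.90 = 11% | 0 |
| 20% | 20% | 0.20/0.80 = 25% | 0 |
| 30% | 30% | 0.30/0.70 = 43% | 0 |

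In a within-group evaluation the whole of this share appears as benefit. In a between-arm comparison with readers masked to arm, the same share is expected in control-period pairs, so the expected difference from this source is b − b = 0.

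**2. The global criterion**

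Let g be the true post/pre ratio of whole-brain perfusion and A the injected activity. The normalisation sentence allows two readings.

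- *Each scan is scaled to the pre-treatment whole-brain level.* The post scan is multiplied by (pre mean / post mean), so the displayed global ratio is 1.00 for every g. This was checked for g = 1.0, 1.1 and 1.3. The increase that grade 3 requires cannot be seen.
- *Both scans are divided by the same pre-treatment value.* The displayed ratio is g × A(post)/A(pre). The permitted range gives 925/1110 = 0.83 to 1110/925 = 1.20 when g = 1. A true increase of 10% can show as 1.1 × 0.83 = 0.92 up to 1.1 × 1.20 = 1.32. No correction for injected activity or for decay over the 40 to 60 minute window is described.

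The ends of that range are extremes. If activities were uniform over 925 to 1110 MBq (an assumption), about 27% of pairs with no true change would show more than +5%, and about 11% more than +10%. Grade 3 also requires fewer or smaller defects. With b = 20% and independence (both assumed), a false grade 3 would arise in about 0.20 × 0.11 = 2% of stable pairs at a +10% visual threshold, or 0.20 × 0.27 = 5% at +5%.

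**3. Masking**

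The imaging section lists two things hidden from readers: laboratory data and clinical data. The grading words describe reduction and increase, and these can be applied only by someone who knows which scan is the earlier one. The pair is also processed relative to the pre-treatment scan. Known order is therefore a strong inference, though not a stated fact. How control-period pairs are labelled is not stated either, since they contain no post-treatment scan. The complete blinding asserted under Randomization does not follow from the procedure described.

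**The case against.** There are five points on the other side.

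- *The trial has an untreated control.* The same scale applied to control-period pairs shows how often improvement is recorded by chance, and the randomised comparison largely removes it. This stands, provided that readers are masked to arm. It does not help the within-group evaluation that the Randomization section relies on, and it does not make worsening visible.
- *No sentence says that readers are told the scan order.* This is correct, and a reader who infers that the protocol specifies open reading goes too far. What stands is that masking to order is not described and that the grading task presupposes the order. Knowing the order is also not the same as knowing the arm.
- *Injected activity cannot create a grade 3.* This is correct. It can only move a pair already judged improved from grade 2 to grade 3. A reader might infer that grade 3 does not measure perfusion at all, but its defect component does. A correction applied and not described would weaken the second reading of the normalisation, but not the first.
- *The noise rates are invented, and two readers with joint resolution reduce noise.* Both are fair. The size is illustrative and the direction is not. Spurious improvement is certain only where visible noise exists, so it should not be called guaranteed.
- *SPECT does not decide the trial.* The sample size, hypotheses and success rule in the statistical section rest on Mindstreams alone. This stands and limits the severity.

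**Conclusion.** The point holds as a defect in how a listed primary endpoint is measured. The missing grade for worsening is explicit in the definitions and needs no assumption. Its effect is to record visible noise as benefit only: for example, 20% improved (worsened pairs scored 1) or 25% (left ungraded) with zero net change, if 20% of stable pairs look better and 20% worse. The damage falls on the within-group evaluation and on the detection of deterioration.

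A reader might infer that the randomised SPECT comparison is invalid. The documents do not support that, because the chance part is largely common to both arms if arm is masked.

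The global criterion fails under the first reading of the normalisation and is confounded by a factor of 0.83 to 1.20 under the second, unless a correction is applied that the protocol does not describe. The consequence is limited to misallocation between grades 2 and 3. The assertion of complete blinding is unsupported by the reading procedure, although unmasked reading is not stated. The plan should be changed, but nothing in this point alters the declaration of study success as written.

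**What to change.** Replace the scale and the reading procedure before any scan is graded, since the missing direction cannot be recovered later without a re-read.

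- **Scale.** Use signed grades −2, −1, 0, +1, +2, with 0 for no visible difference and the worsening grades mirroring the improvement grades. Define every grade on the number and size of regional defects, and give a rule for pairs in which some defects shrink and others grow. At the least, add one grade for worse.
- **Global criterion.** Remove it from the top grade and normalise each scan to itself. If a global measure is wanted, report it separately from counts corrected for injected activity and decay, because self-normalised images cannot show it.
- **Masking.** Present each pair as A and B in random order, under its own code, with dates and arm removed. Mix control-period and HBOT-period pairs, and unmask the order only after grades are final.
- **Text.** State masking to order and arm in the imaging section, so that the statement under Randomization is true.

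The cost is a changed reading form and image labelling, with the same readers and scans. Adding worsening grades does not by itself lower the share graded improved, but net improvement may look smaller (in the example, 20% − 20% = 0).
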